### 2.2 Randomization, allocation concealment and blinding

These participants will be randomly in a 1:1 ratio to HHXYP treatment group and OC group. An independent statistician will use SPSS software to generate the randomization sequence. The designated researcher in the central structure will prepare the assignments in opaque envelopes in sequence, and inform the researcher of the matching card number either by text message or *via* mobile communication application. To ensure blindness in this trial, both of HHXYP and oryzanol pills were packaged with the same appearance throughout the study process, outcome assessors and the data analysts will be blinded to the group allocation.

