#### 2.3.4 Sample sizes

According to a previous study of peri-menopausal women in China (Zhang et al., 2014), we assumed that the mean ± standard deviation (SD) differences in the change in total KI score of the intervention group and the control group were 9 ± 7 and 3 ± 7. PASS 15 software was used for sample size calculation. We determined a sample size of 30 women for each group, with α equal to 0.05 (two-sided) and β equal to 0.01.

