### 2.5 Outcomes

#### 2.5.1 Primary outcome

The primary outcome of the study is the modified Kupperman Index (KI), which will be measured at baseline and 4, 8, 12, 16 weeks after randomization. The total score of KI is 63. It includes 13 items related to peri-menopausal syndrome, and the severity score of each item ranges from 0 to 3. There were different basic score in each item: hot flashes and sweating = 4; Paresthesia, sleep disorders, nervousness, sexual complaints, urinary tract infection = 2; the other items = 1. Item score = basic score × severity score. Classification standard of disease condition: mild: symptom score <13; moderate: symptom score 14–26; severe: symptom score >27 points.

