### 2.8 Statistical analysis

All data will be statistically analyzed using SPSS 20.0 software by a special analysts who is blinded to this trial. Continuous variables with normal distribution are presented as mean ± standard deviation (SD), and categorical variables are presented as frequency/percentage. All of the analyses will be performed on intention-to-treat (ITT) principle. Pearson’s chi-squared test or Fisher’s exact test are used to compare the frequency of categorical variables. Non-parametric Mann-Whitney test or Kruskal–Wallis test is used to compare data sets involving non-normal distribution. The comparison of continuous variables between groups will be evaluated by variance analysis. The main outcome scales at different time points will be analyzed by repeated measurement analysis of variance (ANOVA). Significance level is set as *p*-value less than 0.05.

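### The primary outcome (KI at four post-baseline visits) has no primary visit, and no deciding test ties the repeated-measures ANOVA to the single change contrast behind the sample size

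*Protocol article*

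**What the plan says.** - **Outcome.** Section 2.5.1 states: "The primary outcome of the study is the modified Kupperman Index (KI), which will be measured at baseline and 4, 8, 12, 16 weeks", counted from randomisation. The Abstract and Table 1 give the same visits. Neither they nor Section 2.5.1 single one out. Treatment lasts 12 weeks and follow-up 4 weeks, so the week-16 KI is measured after treatment has ended.
- **Sample size.** Section 2.3.4 assumes that the "differences in the change in total KI score of the intervention group and the control group were 9 ± 7 and 3 ± 7". The resulting size is given as follows: "We determined a sample size of 30 women for each group". The error rates used are stated in the same sentence: "with α equal to 0.05 (two-sided) and β equal to 0.01". No visit is attached to the change.
- **Analysis.** Section 2.8 states: "The main outcome scales at different time points will be analyzed by repeated measurement analysis of variance (ANOVA". A separate sentence there sends between-group comparisons of continuous variables to analysis of variance, without naming a visit or saying whether raw scores or changes are compared. The threshold is p < 0.05. The section does not say which model term decides, whether baseline is a repeated level or a covariate, or how several results would be ordered or adjusted.

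**The concern.** The time point is part of the definition of a primary outcome. Here there are four candidates. The repeated-measures ANOVA adds a group effect and a group-by-time interaction, and KI also falls under the general analysis-of-variance sentence. These tests answer different questions:

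- The group effect compares averages over visits. If baseline is one of the levels, that average includes a visit at which randomisation makes the expected difference zero. It also includes week 16, off treatment.
- The interaction asks whether the two time profiles differ in any way.
- Only a comparison of change at one visit is the quantity used to size the trial.

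Two things are at stake. If the choice among visits and terms is made after the results are seen, the 5% error rate is not protected. And the power of the trial cannot be known until the test is named.

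**Working it through.** **Inputs from the protocol article.** Difference in KI change 9 − 3 = 6; SD of change 7 in each arm; 30 per group, 1:1; two-sided α 0.05; β 0.01.

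**Assumptions made here, not in the document.** Compound symmetry with between-visit correlation ρ of 0.3, 0.5 or 0.7 (0.8 also for the error rate); visit SD σ = 7/√(2(1−ρ)), so that the SD of change stays at 7; no dropout; and the effect profiles given below.

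**1. The plan's own figure.** n per group = 2(z₀.₉₇₅ + z₁₋β)² × 7²/6².
- β = 0.01: 2 × (1.960 + 2.326)² × 49/36 ≈ 50.01, so 51 per group, not 30.
- β = 0.10: 2 × (1.960 + 1.282)² × 49/36 ≈ 28.6, so 29 per group, or 30 with the t distribution.

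For one pre-named change contrast, SE = 7 × √(2/30) = 1.807 and 6/1.807 = 3.32. Noncentral-t power is 90.4%. This is the fair benchmark for 30 per group; it is not the 99% that β = 0.01 implies.

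**2. Type I error.**
- A single named test, group effect or interaction: 4.8–5.1% in 20,000 simulated trials, so 5% holds.
- Group effect or interaction, whichever is significant: 9.5–9.7%.
- Any of four visits, raw scores: 15.5%, 14.5%, 13.1% and 11.4% at ρ = 0.5, 0.6, 0.7 and 0.8; about 17% at ρ = 0.3.
- Any of four visits, change scores: about 16% whatever ρ is. Changes from a shared baseline have covariance σ²(1−ρ) and variance 2σ²(1−ρ), so their correlation is always 0.5.

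**3. Group main effect with baseline as a level.** The difference tested is the mean over five visits. Its SD within an arm is σ√((1+4ρ)/5). At ρ = 0.5, σ = 7, the SD is 7 × √(3/5) = 5.42 and the SE is 5.42 × √(2/30) = 1.40.

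A constant 6 at every post-baseline visit averages (0 + 4 × 6)/5 = 4.8. That is the most it can be if the effect never exceeds 6. Profile 0, 2, 4, 6, 3 averages 15/5 = 3.0; profile 0, 2, 4, 6, 6 averages 18/5 = 3.6.

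| Profile at weeks 0, 4, 8, 12, 16 | Mean difference | Power ρ = 0.3 | ρ = 0.5 | ρ = 0.7 |
|---|---|---|---|---|
| 0, 6, 6, 6, 6 | 4.8 | 99.7% | 92.1% | 64.1% |
| 0, 2, 4, 6, 6 | 3.6 | 93.7% | 71.5% | 41.3% |
| 0, 2, 4, 6, 3 | 3.0 | 82.9% | 55.9% | 30.6% |

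The table shows a spread, not bounds. If the effect vanishes off treatment (0, 2, 4, 6, 0), the mean is 2.4 and power at ρ = 0.7 is 21%.

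**4. The other readings.**
- Group effect without baseline as a level, effects 2, 4, 6, 3: 93.9%, 73.3% and 43.5% at ρ = 0.3, 0.5 and 0.7.
- Group-by-time interaction: 93.3% for the constant profile, 91.8% for 0, 2, 4, 6, 6 and 80.2% for 0, 2, 4, 6, 3, at each ρ.
- Change at week 12: 90.4% in all three tabulated profiles, since each has 6 points at week 12.

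**The case against.** The strongest reply is that the article does not say what a harsh reader would have it say.

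- A reader might infer that the ANOVA group effect does average in baseline. Section 2.8 refers only to different time points. Baseline as a level is the natural reading, because baseline is a listed KI time point and no covariate is named, but it is not stated. Nor is the group effect named as the test. If the interaction decides, this dilution does not arise.
- A reader might infer that success may be claimed on any visit or either F-test, so that the 5% level is already lost. No such rule is written. Any one pre-named test holds 5%; inflation needs a free choice, which the text leaves open but does not prescribe.
- A reader might infer that power is far below plan. It is undetermined. With a constant effect and ρ = 0.3 or 0.5, the group effect has more power than change at one visit. The profiles and correlations are assumptions.
- The general analysis-of-variance sentence, applied to change at one visit, would match the sized contrast.
- Baseline handling, model terms and multiplicity rules are often left to a statistical analysis plan, and one may exist.

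All of this stands as a limit on the claim. It does not remove the gap. The general sentence names no visit either. And the article itself fixes the outcome, the sample size and the analysis, in three sections that cannot be joined into one hypothesis.

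**Conclusion.** The concern holds in conditional form. The article names no primary visit and no deciding term, so the analysis in Section 2.8 is not tied to the one change contrast in Section 2.3.4. Two consequences follow:

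- **Error rate.** It exceeds 5% only if more than one visit or term may count: nearly 10% for group effect or interaction, and about 11–16% for any of four visits with ρ from 0.8 to 0.5.
- **Power.** It depends on the term chosen. For the group effect with baseline as a level it runs from about 31% to 99.7% across the tabulated profiles, against 90.4% for change at one visit.

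These sizes rest on compound symmetry, the assumed correlations and profiles, and no dropout. The absence of a named visit and test rests on the text alone. Naming them will not deliver 99% power: with these inputs that needs 51 per group.

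**What to change.** Before unblinding, state that the primary endpoint is the between-group difference in change in total KI from baseline to week 12 (end of treatment), tested two-sided at α 0.05 and preferably adjusted for baseline KI. Make weeks 4, 8 and 16 and the time profile secondary. Say in Section 2.3.4 that 9 against 3 refers to week 12, and correct either β or the sample size so that the two agree.

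Under the assumptions above, baseline adjustment would give about 98%, 97% and 94% power at ρ = 0.3, 0.5 and 0.7 for a 6-point week-12 difference with 30 per group.

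Naming the visit and the contrast costs only wording, in the protocol and wherever else the primary outcome is recorded. The price is that the other visits lose confirmatory status. Nine women were enrolled by 1 June 2022 and the analyst is to be blinded, which favours an early change. The article cannot show whether that window is still open. A change made after unblinding would have to be reported as post hoc.

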### 2.9 Quality control

In order to guarantee the quality of trial, all investigators are asked to attend special training includes how to fill in the Case Report Form, how to record adverse reactions, how to teach the patients to take medicine, and other details of this trial.

### 2.10 Trial status

The participants are currently being recruited for the present study. Thirty-four patients have entered the screening period and nine patients have been enrolled until 1 June 2022.

## 3 Discussion

TCM has been widely used to treat PMPS for thousands of years in China (Fu et al., 2016). Recent years, it is increasingly popular abroad and thought to offer a personalized alternative to HRT (Johnson et al., 2019). The TCM believes that kidney deficiency is the foundation of peri-menopausal syndrome. As women enter the peri-menopausal period, the kidney’s reservation of Qi gradually decreases, resulting in decreased ovarian function and hormone levels, then causes VMS, such as hot flashes and night sweats. In addition, kidney deficiency also fails to nourish the viscera and meridians, leading to liver-qi stagnation and blood stasis. The function of the liver-qi mainly reflected in adjustment of spirit and emotion. Liver-qi stagnation and blood stasis are the important pathogenesis according to the theory of TCM. Its external manifestations are PMD include anxiety, depression, and other emotional disorders. Therefore, soothing and regulating liver-qi, activating blood and resolving stasis may be an important way to improve VMS and depression of peri-menopausal syndrome.

Honghua Xiaoyao Pill (HHXYP) is a Chinese patent medicine, which is used to sooth liver-qi stagnation, activating blood and resolving stasis. It is modified from Xiaoyao pills (wan), a prescription in Treatise on Febrile Diseases (*Shang Han Lun*). On the one hand, a study shows that Xiaoyao san played an anti-depression role by regulating the tryptophan-kynurenine metabolic pathways in depressed rats (Wang et al., 2018
). Xiaoyao pills also has anti-inflammatory effect, which may relieve depression symptoms by inhibiting inflammatory reaction or activating NGF/BDNF-TRKA/TrkB-CREB pathway (Fang et al., 2020). On the other hand, Xiaoyao pills could reduce the level of inflammatory cytokines, enhance the expression of neurotrophic factors and synaptophysin to inhibite the behavior abnormality of LPS-induced depression-like model rats (Shi et al., 2019). Furthermore, Xiaoyao pills has antioxidant and neuroprotective effects on both cortical and hippocampal regions, which can improve depression-like behavior and oxidative stress of olfactory bulb excised rats by activating PIK3CA-AKT1-NFE2L2 BDNF signaling pathway (Ji et al., 2021). Therefore, it is reasonable to speculate that HHXYP has the effects of regulating anxiety and depression, anti-inflammation, and anti-oxidative stress. HHXYP has been reported as a complementary and alternative therapy for the treatment of gynecological diseases such as irregular menstruation, polycystic ovary syndrome and mastitis (Li 2014; Yan et al., 2020). There are also some researches indicated that it could alleviate peri-menopausal depression, insomnia and other peri-menopausal symptoms. HHXYP combined with estradiol tablets/estradiol dextroprogesterone tablets significantly reduced the modified KI, MENQOL score and serum FSH, LH levels, but increased serum E2 levels compare with estradiol tablets/estradiol dextroprogesterone tablets alone (Hai et al., 2021). HHXYP combined with Wenjing Decoction effectively improved the ovarian function and insomnia in patients with peri-menopausal syndrome compare with HHXYP alone (Zhang et al., 2015). HHXYP combined with conventional treatment (psychotherapy, vitamin D supplementation, HRT) improved Kupperman score and E2 levels compare with conventional treatment (Li et al., 2015). Based on the clues of clinical application and the theory of TCM, HHXYP seems show potential for treating PMPS. However, randomized controlled trials are still needed to determine. Therefore, this study will evaluate the efficacy of HHXYP for hot flash reduction, emotion improvement, and QOL improvement in PMPS patients. In order to better recruit participants, we set the age range between 45–60, as according to some reports, peri-menopause generally occurs around the age of 50 years, with a range between 40 and 60 years worldwide (Li et al., 2016).

In addition to using the KI, MENQOL, HAMD, and HAMA to evaluate the clinical efficacy, we will try to explore the possible mechanism of HHXYP treatment for PMPS by testing monoamine neurotransmitter and vascular vasomotor factor levels. As we known, vasomotor symptoms, such as hot flashes, is associated with increased risk of cardiovascular disease (Santoro, 2016). Serum nitric oxide (NO), a vascular vasomotor factor, plays a central role in the process of estrogen-induced cardioprotection. The increase of its concentration is associated with peri-menopausal status. The increase in plasma endothelin-1 (ET-1) is thought to reflect a rise in vascular production of the peptide in response to the impaired production of NO by endothelial cells (Beppu et al., 2002). Calcitonin gene-related peptide (CGRP) is another potent vascular vasomotor factor that plays an important role in maintaining vascular homeostasis. Both ET-1 and CGRP maintain balance in the body and regulate the vascular elasticity to maintain the systolic and diastolic function of local blood vessels. On the other hand, It is believed that changes in the levels of neurotransmitters, such as norepinephrine (NE), dopamine (DA), and serotonin (5-HT), are related to the occurrence of PMD. Studies have shown that the reduced of E2 level in women with PMD leads to a decrease in the expression of 5-HT, DA, and NE, while antidepressant effects can be achieved by adjusting the levels of 5-HT and DA (Schneider-Matyka et al., 2021). In recent years, it has been found that PI3K/AKT signaling pathway plays an important role the pathogenesis of peri-menopausal depression, which has been a close relationship with vascular factor (Cao et al., 2019; D'Antoni et al., 2017). We will try to explore the molecular mechanism of HHXYP in improving depression and hot flash in PMPS from PI3K/Akt signaling pathway.

Nevertheless, our study still has limitation. Firstly, placebo control is not set because of the potential harm of uncontrolled peri-menopausal syndrome. It might not be accurate enough to reflect the therapeutic effects of HHXYP. Secondly, our purpose is to clarify HHXYP therapeutic effect rather than a placebo effect, which that requires a positive drug as the control group. However, we didn’t use HRT as a drug control because the ethics committee considered that it might be carcinogenic to peri-menopausal women. Oryzanol is a kind of autonomic agent, which is widely used in the adjuvant treatment of insomnia, anxiety and depression in peri-menopausal women (Fujii et al., 2018). The mechanism study shows that oryzanol can increase the release of catecholamine related relatives in limbic system through the blood-brain barrier, which may be related to the improvement of stress (Fujii et al., 2018). In addition, some studies have found that oryzanol also has anti-inflammatory and antioxidant effects (Minatel et al., 2016; Ramazani et al., 2021). These effects are similar to the pharmacological effects of HHXYP, so we choose oryzanol, a recommended supplement in improving PMPS, as the control drug.

In conclusion, the results of this trial will help us to evaluate the efficacy, safety and possible mechanism of HHXYP in treating PMPS.
